## Abstract

**Background:**

We have been investigating an ecologically valid strategy-training approach to enable adults with executive dysfunction to attain everyday life goals. Here, we report the protocol of a randomized controlled trial of the effects of this training compared to conventional therapy in a sample of community-dwelling adults with acquired brain injury and/or stroke.

**Methods/design:**

We will recruit 100 community-dwelling survivors at least six months post-acquired brain injury or stroke who report executive dysfunction during a telephone interview, confirmed in pre-training testing. Following pre-training testing, participants will be randomized to the ecologically valid strategy training or conventional therapy and receive two one-hour sessions for eight weeks (maximum of 15 hours of therapy). Post-testing will occur immediately following the training and three months later. The primary outcome is self-reported change in performance on everyday life activities measured using the Canadian Occupational Performance Measure, a standardized, semi-structured interview. Secondary outcomes are objective measurement of performance change from videotapes of treatment session, Performance Quality Rating Scale; executive dysfunction symptoms, Behavioural Rating Inventory of Executive Function – Adult; participation in everyday life, Mayo-Portland Adaptability Inventory Participation Index; and ability to solve novel problems, Instrumental Activities of Daily Living Profile.

**Discussion:**

This study is of a novel approach to promoting improvements in attainment of everyday life goals through managing executive dysfunction using an ecologically valid strategy training approach, the Cognitive Orientation to daily Occupational Performance. This study compares the efficacy of this approach with that of conventional therapy. The approach has the potential to be a valuable treatment for people with chronic acquired brain injury and/or stroke.

**Trial registration:**

clinicaltrials.gov, Trial Identification Number:
NCT01414348

## Background

Executive processes, that is high-level cognitive functions involved in control and direction of action, including planning, monitoring, initiating, and switching, have been described by Lezak as being the heart of all socially useful, personally enhancing, constructive and creative activities
[1]. Thus, impairments of executive function can have the most devastating impact on everyday life because of their super ordinate role in behavioural and cognitive processing
[2]. Considerable attention has been directed at developing and testing interventions to manage these impairments; in the past six years, four systematic reviews and one meta-analysis related to treatment for executive dysfunction have been published
[3]–
[6].

The majority of studies in this area use some form of problem-solving or metacognitive strategy instruction. Meta-cognitive strategy instruction has roots in cognitive-, educational- and neuro-psychology
[7]–
[9]. Luria, in his seminal work, was perhaps the first to hypothesize explicit steps in the problem-solving process: problem representation, planning, execution and evaluation
[8]. Across the work done in this area, different aspects of the process have been emphasized and, in some cases, additional steps have been included. For example, Levine et al., in a study using metacognitive strategy instruction with adults with traumatic brain injury, emphasize stopping (‘defined as periodic suspension of ongoing activities to assess goal attainment’ , p. 145) as critical for preventing absent-minded slips which would interfere with defining the problem at hand
[10]. In contrast, Rath et al. focused on problem orientation, defined as focusing on removing impediments to effective use of problem-solving skills (i.e., cognitive distortions, misattributions, illogical thinking) to promote effective use of problem-solving skills
[11]. Spikman et al. built on Levine’s work but placed a broader emphasis on self-awareness so that throughout their program participants were asked to predict and then evaluate their successes and/or failures
[12]. In addition, the control condition varied across these studies with only one using conventional therapy, although this study did not report whether they controlled for time spent in therapy, the experimental condition was provided by trained neuropsychologists and the control condition consisted of ‘usual therapy, such as physiotherapy’ (p. 525)
[13]. Despite the differences, as a whole, these studies provide compelling evidence that problem-solving or meta-cognitive training result in positive post-intervention changes including, in some instances, improvements in untrained everyday life activities, suggesting that the training has resulted in participants’ ability to transfer what they have learned to novel, untrained activities
[11]–
[14].

Our pilot work on an ecologically valid approach to strategy-training, an adapted version of the Cognitive Orientation to daily Occupational Performance (CO-OP) approach, also showed changes in everyday life on untrained activities that were maintained at three-month follow-up
[15,16]. The CO-OP approach reflects the understanding of real-world participation posited by the World Health Organization in the International Classification of Functioning
[17], that participation in the real world results from a complex interaction between impairments in bodily structures and functions (e.g., brain pathology), the person’s attributes (e.g., education, intelligence), and the environment within which they are functioning. To be maximally effective, a rehabilitation intervention must address each of these. The CO-OP approach does this by including an explicit metacognitive strategy at its core: this rubric (stated simply as Goal, Plan, Do, Check) is taught to and practiced with patients in the context of their self-identified difficulties in real-world activities and in the environment in which these difficulties occur
[18]. Thus, this approach has maximum ecological validity: rather than simulating real-world activity, the adapted CO-OP approach takes place in the real world, with all of its complexities and demands. Further, it is well suited to reflecting the current health care focus of maintaining people in the community.

The CO-OP approach, like many other rehabilitation interventions, can be considered a complex intervention in that it involves a number of interacting components
[19]–
[21]. A key question identified in relation to evaluating complex interventions is, does the intervention work in everyday practice
[20]? To address this question, we have designed a two-group study for people with acquired brain injury and stroke; the experimental group will receive CO-OP while the control group will receive conventional rehabilitation. Both interventions will be delivered in the community.

### Objective

To discover whether the novel intervention, the adapted CO-OP approach, is more effective than conventional occupational therapy for (a) improving ability to achieve self-identified goals in everyday life; and (b) achieving far transfer demonstrated as overall reduced impact of executive dysfunction in everyday life and overall improved community integration.

## Methods/design

### Design

This study will examine the effects of the adapted form of the CO-OP approach in community-dwelling adults with executive dysfunction arising from acquired brain injury or stroke. Following a telephone-screening interview, participants will attend a baseline testing session and be randomized to the experimental or control interventions. This is a masked trial: participants are told they are receiving one of two forms of rehabilitation therapy both of which will address daily living activities that are difficult to perform. Training, over a 10-week period (up to 15 one-hour sessions), will be followed by post-training and follow-up (3-months) testing.

### Participants and recruitment

One hundred community-dwelling (within the Greater Toronto area) survivors of acquired brain injury or stroke will be recruited (Figure 
1, CONSORT diagram). Participants will be recruited via (1) flyers distributed to a broad network of community agencies providing services to persons with stroke and brain injury; (2) flyers posted on brain injury society and agency websites (e.g., Acquired Brain Injury Network of the Greater Toronto Area); (3) through the Heart and Stroke Foundation Centre for Stroke Recovery research subject pool; and (4) word of mouth. Respondents will be screened via a telephone interview to determine eligibility. Inclusion criteria for the trial are age 18 years or greater; fluent in written and spoken English; have sustained a traumatic brain injury, another form of acquired brain injury that is not related to a congenital, developmental or degenerative disorder but which occurred through a medical problem or disease process (e.g., anoxia, meningitis, subarachnoid haemorrhage, non-malignant tumour removal) and/or cerebrovascular accident; and have evidence of exe-cutive dysfunction on neuropsychological and behavioural testing. Participants must also be able to self-identify areas of day-to-day difficulties that they would like to improve.

**Figure 1 F1:**
[figure not shown]
CONSORT flow diagram.

Exclusion criteria include other significant neurological or psychiatric history (e.g., multiple sclerosis, psychiatric illness requiring hospitalization), concurrent depression (measured using the Centre for Epidemiological Studies Depression Scale)
[22], and/or substance abuse and concurrent receipt of occupational (or similar) therapy services.

We will also recruit a significant other for each participant to answer questions about the impact of executive function impairments on their loved one’s day-to-day life at pre-training, post-training, and follow-up testing.

### Ethical considerations and informed consent

Ethics approval has been received from the Baycrest Research Ethics Board. A trained research assistant will explain the purpose of the study and potential risks to potential participants. Participants will receive an information letter about the study and there will be no time limit for them to consider implications, ask questions, and respond to the invitation to participate. Participants will be informed that they are free to withdraw from the treatment under study at any time for any reason although they will be invited to come back for post-training and follow-up assessments.

### Sample size determination

Our preliminary data with adults with traumatic brain injury divided into a treatment (n = 6) and an inactive comparison group (n = 6) yielded a very large effect size of *d* (standardized difference of means) = 1.22 on self-rated changes in performance on the Canadian Occupational Performance Measure
[23]. The comparison group showed similar performance scores prior to and following the control period (average increase 0.27 ± 0.98) while the intervention group showed an increase between pre-training and post-training testing sessions (average increase 1.69 ± 1.33). We powered this study to detect a moderate effect size as we are comparing the experimental treatment to conventional therapy (as opposed to a no-treatment control group). We are also including a third test session for longer-term follow-up. To achieve 80% power to detect a moderate effect size (*d* = 0.6) with alpha at 5% we need 45 participants per group
[24]. We are over sampling by 10% to account for potential attrition. Thus, we will recruit 50 people for each arm of the study.

### Randomization

Randomization will be done in blocks of four via a random numbers table. Following baseline testing and participant registration, the Research Assistant will open the next sealed opaque envelope.

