### Primary outcome measure

The primary outcome measure is the Canadian Occupational Performance Measure (COPM), a standardized, semi-structured interview
[23], selected as it has been used as the primary outcome measure in previous studies on the CO-OP approach and in other intervention studies with people with acquired brain injury as well as other populations
[29]–
[31]. The COPM interview results in participants identifying specific everyday activities of daily living (including leisure and work-related activities) that they need to, want to, and/or are expected to do, but are having difficulty with. In this study, the COPM will be administered by a trained occupational therapist as part of the pre-training assessment. During the interview, participants will identify five to six areas of everyday life that are problematic and then state these as goals. For example, if someone identifies meal preparation as a problem area, the goal statement might be ‘to prepare dinner for my family three nights each week’. Participants will rate their current performance of each goal on a 10-point Likert type scale (1 = not able to do it all, 10 = able to extremely well).

Prior to the beginning of the training, participants will be asked to select one of the goals for training and the Research Assistant will randomly select two additional goals (of the remaining four or five) for training; thus, three goals will be trained. The remaining goals will not be trained. After goals are identified by participants, their significant other will independently rate their perception of their family member’s performance. The primary outcome is the participants’ self-reported rating of performance for all untrained goals. This score serves as a measure of transfer of training. At post-test and follow-up, participants and their significant others will rate their performance without reference to the ratings done previously.

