## Trial status

This article was submitted on July 4, 2013. To date, 42 participants have been enrolled.

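### One fixed block size of four makes about a third of the allocations deducible in advance by anyone who keeps track of earlier ones

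*Protocol article*

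**What the plan says.** The Randomization section of the protocol article gives one block size and no variation in it: "Randomization will be done in blocks of four via a random numbers table". It then names who reveals the arm, and when: "Following baseline testing and participant registration, the Research Assistant will open the next sealed opaque envelope". No strata are mentioned. The Sample size determination section plans 50 participants per arm, 100 in total.

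Two other sections involve a research assistant. Under Ethical considerations and informed consent: "A trained research assistant will explain the purpose of the study and potential risks to potential participants". Under Primary outcome measure, once the participant has chosen one goal, "the Research Assistant will randomly select two additional goals (of the remaining four or five) for training; thus, three goals will be trained". The goals left over, two or three per participant, form the primary outcome. The timing given for goal selection is before training starts; its order relative to the envelope is not stated.

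On masking, the article describes participants as masked and the raters of the videotaped outcomes as blinded. It states no masking for the Research Assistant, who necessarily sees each allocation when opening the envelope.

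**The concern.** Concealment has to hold for the next participant as well as for the card in the envelope. In short blocks of one constant size, earlier allocations reveal later ones. The person who opens the envelopes in turn sees the whole history, and the block size is easy to know or infer, so for some candidates the arm is known before they are booked.

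What is at stake is selection at entry. A person who knows or can guess the next arm may, even without intent, bring a candidate forward, delay one or encourage one differently. The arms can then differ in ways that randomization was meant to prevent. The planned analysis of covariance adjusts for baseline rating and treatment hours, but not for unmeasured differences in motivation or prognosis that would enter by this route.

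**Working it through.** The article gives no figure for predictability, so there is none to reproduce on this point. The sample size is not in question: d = 0.6 with 80% power and two-sided 5% alpha gives 44.6, so 45 per group by the t-test, and 45/0.90 = 50 per arm.

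**Inputs**
- Block size 4, constant (Randomization section).
- Two participants per arm in each block (assumed from the equal arms of 50).
- One sequence (assumed; no strata are mentioned).
- 100 participants, so 100/4 = 25 blocks.
- An observer who knows all earlier allocations and the block size (assumed).

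**Assignments known with certainty.** The six equally likely orders are AABB, ABAB, ABBA, BAAB, BABA and BBAA. An assignment is certain once one arm has used both its places.
- First and second: never certain.
- Third: certain only in AABB and BBAA, 2/6 = 1/3.
- Fourth: always certain.

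Expected number per block = 0 + 0 + 1/3 + 1 = 1.33. Share = 1.33/4 = 33.3%. Over 25 blocks, 25 × 1.33 = 33.3 participants.

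**Correct best guesses.** The observer names the arm with more places left.
- First: 1/2.
- Second: 2/3.
- Third: (1/3 × 1) + (2/3 × 1/2) = 2/3.
- Fourth: 1.

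Mean = (0.500 + 0.667 + 0.667 + 1.000)/4 = 2.833/4 = 70.8%, against 50% under simple randomization.

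**Would a larger constant block be enough?** The same enumeration gives:

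| Known constant block size | Certain | Best guess correct |
|---|---|---|
| 4 | 33.3% | 70.8% |
| 6 | 25.0% | 68.3% |
| 8 | 20.0% | 66.6% |

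A larger block helps only a little while its size is constant and known. Certainty depends on knowing where the block ends, which varied and undisclosed sizes take away.

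**Do the envelopes prevent this?** They hide the current card until the participant is registered. The deduction uses only cards already opened, so it can be made before the next candidate is booked or registered.

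**The case against.** The strongest reply is that the stated procedure is already protective. The envelopes are sealed and opaque and are opened only once the participant is committed. Eligibility rests on telephone screening and confirmatory testing, and recruitment runs through flyers, websites, a research pool and word of mouth. A constant block of four is a common choice. One third is an upper limit that needs perfect tracking, and no effect on the treatment estimate is shown. All of this stands, and it makes the point modest. It does not remove deduction from earlier allocations.

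A reader might infer four stronger things that the article does not support.

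- **That the untrained goals can be picked to suit the arm.** The article says that "the Research Assistant will randomly select two additional goals (of the remaining four or five) for training". A random draw followed as written cannot favour an arm, even if made after the envelope is opened. The order is unstated rather than wrong, and a condensed article may leave it to the full protocol.
- **That one person both recruits and opens envelopes.** A research assistant explains the study, but the article does not say that this is the individual who opens the envelopes, or that this role decides eligibility.
- **That publishing the block size exposes everyone still to be recruited.** The statement "To date, 42 participants have been enrolled" is dated to submission. The number remaining at publication is not given, and candidates would lack the allocation history in any case.
- **That exchanging one goal alters a third to a half of the primary score.** It replaces one of two or three components. The score moves by the difference between the two goals' ratings divided by 2 or 3, which may be zero.

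**Conclusion.** The point holds for predictability of allocation. With a constant block of four, an observer who tracks earlier allocations can know 33.3% of assignments in advance, about 33 of 100, and guess 70.8% correctly. This assumes equal allocation within blocks, one sequence, complete knowledge of earlier allocations and knowledge of the block size. Incomplete tracking, or several candidates in baseline assessment at once so that the order of opening is not settled, would lower these figures. The direction and size of any resulting bias cannot be derived from the article, and nothing in it suggests that steering took place.

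The goal draw is not an error in the plan. It enters only as a place where one line of procedure would give added protection. Overall this is an inexpensive improvement to a sound basic procedure, not a flaw that invalidates the comparison.

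**What to change.** For participants not yet randomised, replace the remaining envelopes with a list in randomly varied block sizes. Someone outside recruitment should generate and hold it, and the sizes should not be disclosed to site staff. If such a custodian already exists, only the block sizes need to change. Guessing the arm that lags behind will still do better than 50%, but the certain predictions that come from knowing where each block ends should go.

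The cost is one new list and slightly looser balance. The largest possible difference between arms at any moment within a block is half the block size: 2 with blocks of four, 3 with blocks of six, 4 with blocks of eight. No extra participants or staff are needed.

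As a secondary safeguard, add one line to the visit procedure: the participant's own choice of goal and the random draw of the other two are recorded and dated before the envelope is opened. If the full protocol already sets this order, saying so is enough. It would also help to report which order was used for those already enrolled.

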### Measures

All participants will be characterized using socio-demographic (age, gender, education, estimated pre-morbid IQ), event-related (time post-injury/stroke, lesion burden), and neuropsychological status (attention, memory, executive function) variables. Pre-morbid IQ will be estimated using the vocabulary subtest from the WAIS-III
[25]. The neuropsychological test battery will be comprised of tests of (1) attention (Symbol Digit Modalities Test)
[26], (2) memory (Hopkins Verbal Learning Test)
[27], and executive function (Delis-Kaplan Executive Function System, Trail Making, Tower and Verbal Fluency Tests)
[28].

### Primary outcome measure

The primary outcome measure is the Canadian Occupational Performance Measure (COPM), a standardized, semi-structured interview
[23], selected as it has been used as the primary outcome measure in previous studies on the CO-OP approach and in other intervention studies with people with acquired brain injury as well as other populations
[29]–
[31]. The COPM interview results in participants identifying specific everyday activities of daily living (including leisure and work-related activities) that they need to, want to, and/or are expected to do, but are having difficulty with. In this study, the COPM will be administered by a trained occupational therapist as part of the pre-training assessment. During the interview, participants will identify five to six areas of everyday life that are problematic and then state these as goals. For example, if someone identifies meal preparation as a problem area, the goal statement might be ‘to prepare dinner for my family three nights each week’. Participants will rate their current performance of each goal on a 10-point Likert type scale (1 = not able to do it all, 10 = able to extremely well).

Prior to the beginning of the training, participants will be asked to select one of the goals for training and the Research Assistant will randomly select two additional goals (of the remaining four or five) for training; thus, three goals will be trained. The remaining goals will not be trained. After goals are identified by participants, their significant other will independently rate their perception of their family member’s performance. The primary outcome is the participants’ self-reported rating of performance for all untrained goals. This score serves as a measure of transfer of training. At post-test and follow-up, participants and their significant others will rate their performance without reference to the ratings done previously.

